#### 16. CONDITIONS FOR PUBLICATION OF RESULTS

The sponsor and the Researchers are responsible for the publication of the results, both positive and negative, of the trial in scientific journals, in accordance with the provisions of article 39 of RD 1090/2015 and based on the uniform requirements for manuscripts submitted to publicationsbiomedical journals (International Committee of Medical Publication Editors, 2016). The publications generated will be presented to a study writing committee, which will include the sponsors and researchers involved in the study.

The results of this study will be analyzed and published or disseminated in medical journals and/or scientific meetings. The publications generated will be presented to a study writing committee, which will include the sponsors and researchers involved in the study.

## ANNEX 1: SCHEDULE OF VISITS.

[illegible]

|                                         |   |   |   |   |   |   |   |   |   |   |   |   |   |   |   |
|-----------------------------------------|---|---|---|---|---|---|---|---|---|---|---|---|---|---|---|
| AVS Scale                               | X | X |   | X |   | X |   | X |   | X |   | X |   | X |   |
| CIVIQ 20
Questionnaire               | X | X |   |   | X |   | X |   | X |   | X |   |   | X |   |
| Treatment of VU
- BAMS               |   | X | X | X | X |   |   |   |   |   |   |   |   |   |   |
| Pregnancy test                          | X |   |   |   |   |   |   |   |   |   |   |   |   |   |   |
| Sample
Collection -
Exudate Study |   | X | X | X | X | X |   |   |   |   |   |   |   |   |   |
| Adverse events
/ Mortality           |   | X | X | X | X | X | X | X | X | X | X | X | X | X | X |
| Concomitant
medication               | X | X | X | X | X | X | X | X | X | X | X | X | X | X | X |

Protocol code: UV/AP/21 Nx

EudraCT: 2021-001341-12

Version of July 15, 2024.

## ANNEX 2: STANDARD PROCEDURE FOR ADMINISTRATION OF THE INVESTIGATIONAL MEDICINAL PRODUCT.

1. Remove the compression therapy and then the apôsite that covers the injury. Perform the technique carefully, taking care not to damage the wound bed or the perilesional skin.
2. Sample collection of exudate: with filter paper (Fisherbrand™, Fisher Scientific S.L., Madrid, Spain):
  - Exudate samples should be taken from the ulcer bed by absorption with filter paper (500-1000 ul).
  - Place the filter paper over the injury. It is only necessary to place it, it is not necessary to rub.
  - One minute after the application of the absorbent paper, it shall be placed in 0.5 mL of cold phosphate-buffered saline solution.
  - The samples will be stored at a minimum temperature of -20°C until analysis.
3. Cleaning and washing of the wound with normal saline solution (NaCl 0.9%), exerting sufficient pressure to allow the dragging of debris or debris without damaging the wound tissue.
4. Mechanical debridement of devitalised or non-viable areas of scarring:
  - Gently rub the area of the injury on which you want to perform the technique
  - Wash away non-viable tissue debris
  - Perform a second cleaning of the injury with normal saline solution (NaCl 0.9%), exerting enough pressure to allow the debris or debris to be carried away without damaging the wound tissue.
5. Determine the wound area using a graduated ruler, measuring the longest vertical length (length) and the longest perpendicular length (width), multiplying both lengths.
6. Deposit the fibrin matrix · hyaluronic acid on the base of the wound depending on the size of the injury.
  - a) The necessary material for the handling and administration of the matrix is the following:
    - ✓ Sterile cloth
    - ✓ Sterile gloves
    - ✓ Sterile gauze
    - ✓ Normal saline solution (NaCl 0.9%), if necessary

- ✓ Straight blunt tip scissors
  - ✓ Simple sterile dissection clamp
  - ✓ Static demographic marker (Ref. 400133181)
- b) The matrix must remain in cold at all times (2 · 8xC)
  - c) Remove the mesh from the refrigerator
  - d) Ensure a sterile field before handling it
  - e) Keep in mind the area of the injury to calculate the required portion of the matrix
  - f) Open the container where the mesh is deposited once sterility is guaranteed
  - g) With the help of the demographic marker and the ruler included in the same package, mark the matrix area you need according to the area of the injury
  - h) Trim, if necessary, the matrix to fit the wound area
  - i) Carefully pick up the portion of the matrix with the help of the single-dissecting tweezers
  - j) Place the piece of womb on the wound without exerting pressure, making sure that it properly covers the injury and that it is in contact with the wound bed
7. Cover the wound with a non-adhesive secondary polyurethane foam appliance (New Cutimed® Siltec Plus 73288/001).
  8. Jobst® Compri2® 40mmHg multilayer compression therapy of the area where the injury occurs.

### ANNEX 3: STUDY OF EXUDATE

Exudate samples will be stored and analyzed in Laboratory 10.4. Faculty of Health Sciences. University of Granada. [name].

The concentration of IL-4, IL-6, TGF $\gamma$ 1 and IL-10 should be determined in exudate samples collected at the beginning of the study (day 0, visit 2) and at visits 3, 4, 5 and 6. The sample will be collected before cleaning and disinfection of the wound. To this end, samples of at least 500-1000  $\mu$ l of exudate should be taken from the ulcer bed by absorption with filter paper (FisherbrandTM, Fisher Scientific S.L., Madrid, Spain). Samples will be collected at the same point of the ulcer throughout all visits and will be stored at a minimum temperature of -20°C until analysis after homogenization by pipetting and aliquoting. The samples will be analyzed by ELISA, following the manufacturer's instructions, no later than 6 months after collection and freezing of the exudate. The measurements will be carried out in triplicate. The concentration of each of the cytokines will be expressed as picograms per milliliter (pg/ml). In the event that the concentration of cytokines if exudate is less than the detection limit of the ELISA kit, samples may be concentrated if necessary using centrifugation concentration systems (Millipore).

These samples will only be analysed within the framework of this clinical trial, with the surplus being destroyed according to the centre's protocols.

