### 6.3. INCLUSION CRITERIA

To be eligible for inclusion in the study, patients must meet all the inclusion criteria described below:

1. Signing the informed consent (IC) after reading the patient information sheet (HIP).
2. Over 18 years of age of both sexes.
3. Active or recurrent venous ulcer (C6 according to the CEAC clinical classification, Annex 5) in the lower extremity with an area of between 5-10 cm^2.
4. Grade III on the Widmer scale.
5. Distal pulses in palpable lower limbs (tibial and pedium). ABI between 0.8 - 1.3.

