### 10.2. SECONDARY VARIABLES

Effectiveness:

The answer will be analysed through clinical and biological parameters

Clinical variables:

- Percentage of patients who achieve complete healing at 12 weeks of follow-up (complete epithelialization maintained for 2 weeks) when comparing control group versus treatment.
- Time elapsed (days) to wound closure, measured from the start of treatment to the absence of continuity solution (when the wound bed is completely re-epithelialized and with new tissue) when comparing control group versus treatment.
- Percentage of patients who presented better in the total score and by Resvech 2.0 scale (size of injury, depth of affected tissues, borders, type of tissue in the wound bed, exudate, and infection · inflammation) with respect to baseline and when comparing control group versus treatment.
- Percentage reduction in wound extension (relative area, measure, graded rule) with respect to baseline visit and when comparing the control group versus the experimental group.
- Percentage of patients who have a decrease in the score of the AVS pain scale with respect to the baseline visit when comparing the control group versus the experimental group.
- Percentage of patients who perceive better quality of life according to the score obtained in the CIVIQ20 throughout the treatment/follow-up with respect to the baseline visit and when comparing both groups.

Biological variables:

- Evolution of the pattern of cytokines and growth factors obtained from ulcer exudate samples at day 0, +7, +14, +21 and +28 when comparing both groups and their relationship with ulcer healing.

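### Cytokine results in pg/ml depend on an exudate volume that is never recorded, so dilution can confound the comparison of arms and the relation to healing

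*Protocol*

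**What the plan says.** Annex 2, step 2, describes collection: "Exudate samples should be taken from the ulcer bed by absorption with filter paper (500-1000 ul"). It continues: "One minute after the application of the absorbent paper, it shall be placed in 0.5 mL of cold phosphate-buffered saline solution". Annex 3 words the volume differently, beginning "To this end, samples of at least 500-1000" µl, and does not mention PBS. It asks for the same sampling spot at every visit, ELISA in triplicate, and a unit: "The concentration of each of the cytokines will be expressed as picograms per milliliter (pg/ml"). For values under the kit's detection limit, "samples may be concentrated if necessary using centrifugation concentration systems (Millipore").

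Neither annex weighs the paper, records the absorbed volume, or relates the result to volume, total protein or sampled area. Neither says whether the millilitre in the unit is exudate or the mixture of exudate and PBS. No rule covers a sample smaller than the stated volume.

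Section 10.2 uses the values as the biological secondary variable, assessed "at day 0, +7, +14, +21 and +28 when comparing both groups and their relationship with ulcer healing". Secondary objective 3 in Section 4.2 also links them to the other efficacy parameters.

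The PBS step appears only in Annex 2, the procedure for applying the investigational product. Annex 4, the control procedure, has no exudate step. Section 9.6 says that controls are treated alike except for the sheet, so equal handling is probably intended.

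**The concern.** A fixed volume of diluent is added to a variable and unmeasured volume of exudate, so the measured concentration depends on how much fluid the paper took up. Random variation in uptake would only add noise. Here, uptake may follow the state of the wound: the Resvech 2.0 scale (Annex 6, item 5) scores exudate from dry to leaking, so the protocol itself treats exudate amount as something that varies with the ulcer.

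A change in dilution could then be read as a change in cytokines. It could differ between arms if exudate amount differs, and it could create or hide part of the planned association with healing. With 10 patients per arm (Section 5.3), there is little chance of separating the two afterwards.

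**Working it through.** The protocol gives no figure of its own on this point to reproduce. The check is a mass balance.

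**Inputs**
- Diluent: 0.5 mL PBS, fixed (Annex 2).
- Absorbed volume V: 0.5 to 1.0 mL (Annexes 2 and 3).
- Eligible ulcer area: "in the lower extremity with an area of between 5-10 cm"² (Section 6.3).
- Assumption: full recovery of cytokine from the paper.

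**Formula.** With true exudate concentration C, the paper carries C × V, and this is spread over V + 0.5 mL. So

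reading = C × V/(V + 0.5).

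**Within the stated range**
- V = 1.0 mL: 1.0/1.5 = 0.667 of C.
- V = 0.5 mL: 0.5/1.0 = 0.500 of C.
- Ratio: 0.500/0.667 = 0.75. An unchanged cytokine appears to fall by 25%, and two arms with equal C at these two volumes would show a ratio of 0.75.
- Conversely, 0.667/0.500 = 1.33. A true 1.33-fold rise would look like no change.

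**Below the stated range (assumed volumes)**

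| V (mL) | Reading/C | Change from V = 1.0 mL |
|---|---|---|
| 0.25 | 0.25/0.75 = 0.333 | -50% |
| 0.10 | 0.10/0.60 = 0.167 | -75% |

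**Are short samples plausible?** Depth of fluid = volume/area. For 0.5 mL, this is 0.5 mm over 10 cm² and 1.0 mm over 5 cm², the eligibility limits. It is 5 mm over 1 cm², an illustrative area for an ulcer that has nearly closed. The minimum becomes harder to meet as an ulcer shrinks, but the documents do not show what volumes will be obtained.

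**Does the correction work?** Multiplying the reading by (V + 0.5)/V returns C:
- V = 1.0 mL: 0.667 × 1.5 = 1.00.
- V = 0.5 mL: 0.500 × 2.0 = 1.00.
- V = 0.1 mL: 0.167 × 6.0 = 1.00.

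The multiplier of 6 at 0.1 mL also shows that any error in V matters most in the smallest samples.

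The amount per one-minute sample is reading × (V + 0.5) = C × V. It also needs V. It halves when V halves at constant C, so it complements the corrected concentration and cannot replace it.

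**The case against.** Several points on the other side stand.

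- **Denominator.** A reader might infer that the reported figure is certainly an uncorrected concentration of the PBS mixture. The protocol does not say so; Annex 3 speaks of concentration in exudate samples. But converting to exudate needs V, and no step provides it.
- **Direction.** A reader might infer that a healing ulcer will show falling cytokines. That follows only if the absorbed volume drops. Contact time and sampling spot are standardised, and paper that saturates would take up a constant volume. Paper size and capacity are not given, so the course of V cannot be derived.
- **Size.** Falls of 50% or 75% need volumes below the stated minimum. They illustrate what short samples would do and are not expected values.
- **Centrifugal concentration.** A reader might infer that concentrated samples will be reported inflated. Annex 3 does not state a correction, but it does not exclude one, and dividing by the factor is ordinary laboratory bookkeeping. The documents give no factor, so no size can be put on this.
- **Arms.** The idea that the fibrin-hyaluronic sheet itself changes exudate uptake is conjecture; nothing in the documents supports it.
- **Importance.** The main variables are feasibility and safety (Section 10.1). Neither depends on the cytokines.

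A laboratory manual might contain a weighing step, but Annex 3 neither describes nor cites one. It would also be wrong to leave the matter to the analysis plan: this is a quantity to be collected at sampling, and analysis cannot restore it.

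**Conclusion.** The point holds as a weakness in how a secondary biological endpoint is measured. As written, the reading scales with V/(V + 0.5) and V is not recorded. Assuming full recovery from the paper, this allows an apparent fall of up to 25% at constant true concentration if every sample lies between 500 and 1000 µl, and more only if samples fall short. Because exudate amount belongs to the wound assessment, the dilution can confound both the comparison of arms and the relation to healing.

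The documents do not establish how large the effect will be in practice, which way it will go on balance, or whether it will differ between arms. The feasibility and safety conclusions are unaffected. This is a cheap improvement, but it has to be in place before samples are taken.

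**What to change.** In Annexes 2 and 3, with the collection steps stated to apply to both arms:

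1. Weigh the tube of PBS together with its dry paper before sampling, and again once the used paper is in the tube. The gain gives V, taking 1 mg as about 1 µl.
2. Report exudate concentration = ELISA value × (V + 0.5)/V. Give pg per one-minute sample, ELISA value × (V + 0.5), alongside it, because the correction is imprecise at very small V.
3. State that pg/ml refers to exudate.
4. Record any centrifugal concentration factor and divide it out.
5. Replace the minimum that is worded as a range with a single figure, and say how samples below it are handled.

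The cost is two weighings for each of at most 20 × 5 = 100 samples, plus a line on the laboratory worksheet. There is no added visit or patient procedure. Tube handling and evaporation need care where sampling is done at home or in a residence, which Section 6 makes possible. The correction still assumes full recovery from the paper.

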#### ANNEX 4: STANDARD PROCEDURE FOR THE CURE OF UNCOMPLICATED VENOUS ULCERS.

1. Remove the compression therapy and then the apôsite that covers the injury. Perform the technique carefully, taking care not to damage the wound bed or the perilesional skin.
2. Cleaning and washing of the wound with normal saline solution (NaCl 0.9%), with sufficient exertion Pressure so that debris or debris can be carried away without damaging wound tissue.
3. Mechanical debridement of devitalised or non-viable areas of scarring:
  - ✓ Gently rub the area of the injury on which you want to perform the technique
  - ✓ Wash away non-viable tissue debris
  - ✓ Perform a second cleaning of the injury with normal saline solution (NaCl 0.9%), exerting enough pressure to allow the debris or debris to be carried away without damaging the wound tissue.
4. Determine the wound area using a graduated ruler, measuring the longest vertical length (length) and the longest perpendicular length (width), multiplying both lengths.
5. Cover the wound with a New Cutimed® Siltec Plus 73288/001Jobst®
6. Traditional compression therapy (Compri2® 40mmHg multilayer)

## ANNEX 5: BASIC CEAP CLASSIFICATION

### Clinical classification - C

C0: Absence of visible or palpable signs of venous disease C1:

Telangiectasias or reticular veins

C2: Truncal varicose

veins C3: Edema

C4a: Pigmentation and/or eczema

C4b: Lipodermatosclerosis and/or white atrophy

C5: Tissue abnormalities and history of healed venous ulcer C6: Active  
venous ulcer

These sections are accompanied by a subheading S or A:

- S: Symptomatic that includes pain, tightness, skin irritation, heaviness, muscle cramps, as well as any other discomfort attributable to venous dysfunction.
- A: Asymptomatic

### Etiological classification - E

Ec: Congenital

Ep: Primary

Is: Secondary or post-thrombotic

In: Unidentified venous etiology Anatomical

### classification - A

As: Superficial veins

Ap: Perforating veins

Ad: Veins of the deep venous system An:

Unidentified venous location

### Physiopathological classification -

PPr: Reflux

Po: Obstruction

Pr,o: Reflux and obstruction

Pn: Unidentified venous pathophysiology

ANNEX 6: RESVECH 2.0 SCALE

| Items                                                                                                                                                            | Measure 0 | Measure 1 | Measure 2 | Measure 3 |
|------------------------------------------------------------------------------------------------------------------------------------------------------------------|-----------|-----------|-----------|-----------|
| 1. Dimension of the injury                                                                                                                                |           |           |           |           |
| 0. Surface = 0 cm                                                                                                                                    |           |           |           |           |
| 1. Surface < 4 cm                                                                                                                                    |           |           |           |           |
| 2. Surface = 4 ≤ 16 cm                                                                                                                               |           |           |           |           |
| 3. Surface = 16 ≤ 36 cm                                                                                                                              |           |           |           |           |
| 4. Surface = 36 ≤ 64 cm                                                                                                                              |           |           |           |           |
| 5. Surface = 64 ≤ 100 cm                                                                                                                             |           |           |           |           |
| 6. Surface ≥ 100 cm                                                                                                                                  |           |           |           |           |
| 2. Depth/Tissues Affected                                                                                                                                 |           |           |           |           |
| 0. Intact Skin Healed                                                                                                                                            |           |           |           |           |
| 1. Dermis-epidermis involvement                                                                                                                                  |           |           |           |           |
| 2. Involvement of subcutaneous tissues
(adipose tissue without reaching the fascia of the muscle)                                                             |           |           |           |           |
| 3. Muscle involvement                                                                                                                                            |           |           |           |           |
| 4. Involvement of the bone and/or adjoining tissues (tendons, ligaments, joint capsule or black eschar that does not allow you to see the tissues underneath it) |           |           |           |           |
| 3. Edges                                                                                                                                                  |           |           |           |           |
| 0. Indistinguishable                                                                                                                                             |           |           |           |           |
| 1. Diffuse                                                                                                                                                       |           |           |           |           |
| 2. Delimited                                                                                                                                                     |           |           |           |           |
| 3. Damaged                                                                                                                                                       |           |           |           |           |
| 4. Thickened                                                                                                                                                     |           |           |           |           |
| 4. Type of tissue in the wound bed                                                                                                                        |           |           |           |           |
| 4. Necrôtic (dry black eschar or wet)                                                                                                                            |           |           |           |           |
| 3. Necrotic tissue and/or sloughs in the bed                                                                                                                     |           |           |           |           |
| 2. Granulation fabrics                                                                                                                                           |           |           |           |           |
| 1. Epithelial tissue                                                                                                                                             |           |           |           |           |

|                                                           |  |  |  |  |
|-----------------------------------------------------------|--|--|--|--|
| 0. Closure/Healing                                        |  |  |  |  |
| 5. Exudate                                         |  |  |  |  |
| 3. Dry                                                    |  |  |  |  |
| 0. Wet                                                    |  |  |  |  |
| 1. Wet                                                    |  |  |  |  |
| 2. Saturated                                              |  |  |  |  |
| 3. With exudate leakage                                   |  |  |  |  |
| 6. Infection/Inflammation (Biofilm signs)          |  |  |  |  |
| 6.1. Pain that is increasing (Yes=1/No=0)                 |  |  |  |  |
| 6.2. Erythema in the perilesiön (Si=1/No=0)               |  |  |  |  |
| 6.3. Edema in the perilesiön (Si=1/No=0)                  |  |  |  |  |
| 6.4. Temperature increase (Si=1/No=0)                     |  |  |  |  |
| 6.5. Exudate that is increasing (Yes=1/No=0)              |  |  |  |  |
| 6.6. Purulent exudate (Si=1/No=0)                         |  |  |  |  |
| 6.7. Friable or easily bleeding fabric
(Yes=1/No=0)    |  |  |  |  |
| 6.8. Wound Stagnant what no
Progresses
(Yes=1/No=0) |  |  |  |  |
| 6.9. Biofilm compatible fabric (Si=1/No=0)                |  |  |  |  |
| 6.10. Odor (Yes=1/No=0)                                   |  |  |  |  |
| 6.11. Hypergranulation (Si=1/No=0)                        |  |  |  |  |
| 6.12. Increased wound size
(Yes=1/No=0)                |  |  |  |  |
| 6.13. Satellite lesions (Yes=1/No=0)                      |  |  |  |  |
| 6.14. Tissue pallor (Si=1/No=0)                           |  |  |  |  |

